**Methods:**

Stage 0/I/II melanoma patients (*n* = 600) from dermatology, surgical, or general practice clinics in NSW Australia, will be randomised (1:1) to the intervention (patient-led surveillance, *n* = 300) or control (usual care, *n* = 300). Patients in the intervention will undergo a second randomisation 1:1 to polarised (*n* = 150) or non-polarised (*n* = 150) dermatoscope. Patient-led surveillance comprises an educational booklet, skin self-examination (SSE) instructional videos; 3-monthly email/SMS reminders to perform SSE; patient-performed dermoscopy with teledermatologist feedback; clinical review of positive teledermoscopy through fast-tracked unscheduled clinic visits; and routinely scheduled clinic visits following each clinician’s usual practice. Clinician-led surveillance comprises an educational booklet and routinely scheduled clinic visits following each clinician’s usual practice.

The primary outcome, measured at 12 months, is the proportion of participants diagnosed with a subsequent new primary or recurrent melanoma at an unscheduled clinic visit. Secondary outcomes include time from randomisation to diagnosis (of a subsequent new primary or recurrent melanoma and of a new keratinocyte cancer), clinicopathological characteristics of subsequent new primary or recurrent melanomas (including AJCC stage), psychological outcomes, and healthcare use. A nested qualitative study will include interviews with patients and clinicians, and a costing study we will compare costs from a societal perspective. We will compare the technical performance of two different models of dermatoscope (polarised vs non-polarised).

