#### Secondary objectives

To assess the impact of patient-led vs clinician-led surveillance on:
Time from randomisation to diagnosis of a subsequent new primary or recurrent melanoma and of a keratinocyte cancer.Psychological outcomes using validated scales for fear of new or recurrent melanoma, general anxiety, stress, and depression.Skin self-examination:I.confidence in, knowledge of, attitudes to, and beliefs about skin self-examination;II.adherence to recommended skin self-examination practice.4.Acceptability of a reduction in routinely scheduled clinic visit frequency.5.Resource use through measurement of:I.number of lesions surgically excised;II.number of follow-up visits attended (both scheduled and unscheduled).

And to:
6.Evaluate the technical performance of two different models of mobile dermatoscope, which patients can attach to their smartphones.7.Assess the acceptability of patient-led surveillance to patients and clinicians (nested qualitative study).8.Assess resource use and costs for healthcare system, patient, and environment (costing study).

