##### Intervention description {11a}

Trial participants in the control arm will receive clinician-led surveillance (usual care), which involves:
An educational booklet ‘Your guide to early melanoma’;Routinely scheduled clinic visits as recommended by their treating clinician (likely to be at intervals between 6 and 12 months);Unscheduled clinic visits, if needed (not prompted through teledermatology)

Trial participants in the intervention arm will receive the intervention (patient-led surveillance) as an adjunct to their usual care, including:
An educational booklet ‘Your guide to early melanoma’;Routinely scheduled visits as recommended by their treating clinician;Unscheduled clinic visits, if needed (not prompted through teledermatology);Continued access to the ASICA skin checker instructional videos on how to perform SSE (including checking for locoregional recurrence) [30, 39];A mobile dermatoscope (with a polarised or non-polarised light source) to attach to their phone, with detailed written and video instructions on how to use the smartphone app and dermatoscopeTraining for themselves and a partner/friend/support person in using the dermatoscope and app, delivered one-on-one by web conferencing;Email or SMS text reminders every 3 months to perform SSE;Teledermatology (see Fig. 2)

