#### Secondary outcomes

(M2) Time to diagnosis of a new skin cancer: time from randomisation to the histopathology diagnosis of a melanoma or keratinocyte skin cancer (as defined by the date on the histopathology report).

(M3) Pathological characteristics of new skin cancers: including thickness, stage, and other prognostic factors (melanomas and keratinocyte skin cancers).

(M4) Skin Self Examination (SSE) including:

M4.1. Thoroughness, confidence, beliefs, attitude, and knowledge of SSE will be assessed by items adapted from Janda et al. [42].

M4.2. Adherence with recommended SSE practice (total body self-examination conducted three-monthly); Participants will be asked how often they perform a complete examination of their skin.

(M5) Fear of new or recurrent melanoma (FCR) severity: assessed using a modified (i.e. melanoma-specific) version of the 9 item FCR Inventory severity subscale, the most comprehensive multi-dimensional scale of FCR available [10]. A higher score indicates greater FCR.

(M6) General anxiety, stress and depression: measured using the short version of the Depression Anxiety and Stress Scales (DASS-21) [43]. The DASS-21 is a set of three 7-item self-report scales designed to measure the emotional states of depression, anxiety, and stress.

(M7) Acceptability of hypothetical reduction in scheduled clinic visit frequency: measured through questionnaire items designed specifically for this study.

(M8) Number of lesions surgically evaluated: measured through interrogation of clinic data.

(M9) Number of clinic visits attended: (routinely scheduled and fast-tracked unscheduled clinic visits) measured through clinic data.

(M10) Resource use: Costs to the health system and to patients in each arm of the trial will be estimated using an online resource use diary. The diary will be used to document and measure health service use - such as doctors’ clinic visits, other health practitioner consultations, imaging and other tests, hospital visits, and time taken to take and submit images for teledermatology. The diary will also document days out-of-role (including paid and unpaid work) and travel costs. The diary will be based on existing resource use questionnaires and the patient diary used in the MEL-SELF pilot study.

(M11) Carbon emissions: carbon costs of resources used, estimated using established carbon accounting methods [35, 36].

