##### Patient diaries

Patient out of pocket and health system costs associated with each arm of the trial will be estimated using an online monthly resource use diary [51, 52]. The diary will be used to document and measure health service use - such as melanoma clinic visits, other health practitioner consultations, imaging and other tests, hospital visits, and time taken to take and submit images for teledermatology. We will ask patients to report the number of trips made to their melanoma follow-up clinic and the mode of transport used. We will also ask patients to report any visits to other physicians for a skin lesion excision or other skin cancer-related procedures. The time each patient spends to take and submit images, and check teledermatology reports (intervention group) will be recorded. The diary will also document informal caregiver (carer) days out-of-role (including paid and unpaid work), travel costs and direct carer costs.

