##### Linkage

At completion, trial data will be linked with site databases for a schedule of clinic appointments, procedures, and pathology, and with the New South Wales (NSW) Cancer Registry and the Medicare Benefits Schedule claims database.

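### The lesion count (M8) is defined from clinic data although outside excisions are expected and the intervention steers lesions to the clinic, so capture may differ by arm

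*Protocol article*

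**What the plan says.** Secondary objective 5 measures resource use through two counts, the first being the "number of lesions surgically excised". The matching outcome under Outcomes {12} is "M8) Number of lesions surgically evaluated: measured through interrogation of clinic data". No other source is named for it. The visit count is likewise "routinely scheduled and fast-tracked unscheduled clinic visits) measured through clinic data".

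Other sections show that care outside the recruiting clinics is foreseen and recorded. Under Patient diaries: "We will also ask patients to report any visits to other physicians for a skin lesion excision or other skin cancer-related procedures". Under Linkage, trial data are joined with site databases and "with the New South Wales (NSW) Cancer Registry and the Medicare Benefits Schedule claims database". Section {26b} seeks consent for other doctors, hospitals and laboratories to release information, and a separate specific consent for Medicare claims. Under Pathology, study staff confirm lesion counts from participants' medical records.

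On routing, the Abstract describes "clinical review of positive teledermoscopy through fast-tracked unscheduled clinic visits" as part of the intervention. The Intervention description {11a} gives both arms the option of "Unscheduled clinic visits, if needed (not prompted through teledermatology").

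**The concern.** M8 is one of only two measures named for objective 5, and it is a natural place to look for extra surgery caused by patient-led surveillance. A count taken from one place of care is a fair comparison only if the same share of excisions happens there, or is recorded there, in both arms. The intervention is built to bring patient-found lesions to the treatment centre. A control participant who finds a lesion may use an unscheduled visit at the same clinic, but nothing in the trial prompts it, and another doctor may remove the lesion instead.

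If clinic data miss more control-arm excisions, patient-led surveillance will appear to cause more surgery than it does. The Poisson regression planned for counts cannot repair this, because excisions that never reach the data leave no trace in the model.

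The count is also described in three ways: lesions excised (Secondary objectives), lesions surgically evaluated (M8), and lesions biopsied or removed (Pathology). An excision count and a biopsy-plus-excision count are different quantities.

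**Working it through.** The documents state no figure for M8, so there is none to reproduce, and no sample-size figure depends on it. The check has two parts.

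**1. Does the definition leave outside excisions out?**
- M8 names clinic data. M10, in the same list, names the diary. The diary is thus assigned to M10 and not to M8.
- Participant retention and withdrawals {18b} lists clinic, Cancer Registry and Medicare claims data as separate sources, and End of study does the same. In the protocol's own usage, clinic data do not include Medicare claims.
- The diary item on other physicians shows that outside excisions are expected.

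As written, M8 is therefore narrower than the data the trial collects.

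**2. What would unequal capture do?**
Let R be the true rate ratio (intervention to control), and let c_I and c_C be the fractions of all excisions that clinic data capture in the intervention and control arms. Then

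observed ratio = R × (c_I / c_C).

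The documents give neither fraction. The values below are assumptions, with R = 1.

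| c_I | c_C | Observed ratio |
|---|---|---|
| 0.95 | 0.90 | 0.95/0.90 = 1.06 |
| 0.95 | 0.80 | 0.95/0.80 = 1.19 |
| 0.90 | 0.70 | 0.90/0.70 = 1.29 |
| equal | equal | 1.00 |
| 0.80 | 0.90 | 0.80/0.90 = 0.89 |

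Incomplete capture alone does no harm to the ratio; only a difference between arms does. The error can run either way.

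On whether a difference is plausible, the Sample size section expects 6% against 1% of participants to have a melanoma diagnosed through an unscheduled visit, and places that visit at the treatment centre. Those are diagnoses, not excisions, so they give no capture fraction. They do show that drawing patient-found lesions into the clinic is an intended effect of the intervention.

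**The case against.** The strongest reply is that bias is not shown. No passage says that control participants go elsewhere more often. To be eligible, every participant must have a routine visit booked at a recruiting centre, and both arms have scheduled and unscheduled visits there. The Primary objective also credits the control arm with the treating doctor's usual fast-track processes. This stands: a reader might infer that M8 is biased against the intervention, but the documents support only that it may be biased, in an unknown direction.

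Second, M8 does not say clinic data alone, and the medical-record review under Pathology may pick up some outside excisions. This stands in part. Records can narrow the gap, but the definition does not say that outside lesions count, and elsewhere the article treats clinic data as distinct from claims.

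Third, care elsewhere already enters M10 through the diary in both arms. That protects the costing comparison. It does not help objective 5, which rests on M8 and M9.

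Fourth, a reader might infer that M9 is wrong for the same reason. The article does not support that: "M9) Number of clinic visits attended: (routinely scheduled and fast-tracked unscheduled clinic visits) measured through clinic data" is by name a count of clinic visits, and clinic data are its natural source. Widening it to all providers would make a different outcome.

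Fifth, the separate statistical analysis plan may settle the detail. It may, but the article defers analysis methods to that plan while fixing the outcome and its source itself.

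**Conclusion.** The point holds for M8 as a risk of unequal ascertainment. The count is tied to clinic data, outside excisions are anticipated, and one arm is actively steered to the clinic. Size and direction are unknown: over the assumed capture fractions above, a true ratio of 1 would be observed as anything from 0.89 to 1.29, and equal capture would leave it at 1.00. These values illustrate sensitivity and are not evidence that bias is present.

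The conclusion rests on reading clinic data as excluding Medicare claims and the diary, which is how the article uses the term elsewhere. The broader claim that the trial's resource comparison as a whole is biased is not supported, because M10 draws on the diary and M9 is properly a clinic count. The three descriptions of the lesion count are a plain inconsistency and should be reconciled whatever is decided about sources.

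**What to change.** - Use one definition in Secondary objectives, Outcomes {12} and Pathology: lesions biopsied or excised, at any provider, within 12 months of randomisation. The window needs stating because linked data are collected to 24 months.
- Ascertain M8 identically in both arms from clinic and pathology records plus linked Medicare claims. Use the diary to flag outside procedures for confirmation, and remove duplicates across sources.
- Report the clinic-only count alongside as a sensitivity result. A clear difference between the two ratios would show how much the choice of source matters.
- Report Medicare consent and diary completion by arm.
- Keep M9 as a count of clinic visits from clinic data, and report outside skin-related visits from the diary and claims beside it.

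The cost is revised wording and data merging; the sources and consent provisions are already in the protocol. There are three downsides. M8 must wait for linkage. Claims cover only participants who gave the specific Medicare consent. Diary reporting in an open-label trial may itself differ by arm, which is why the diary should prompt confirmation and not count on its own.

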### Participant timeline {13}

The components and timing of enrolment activities, interventions, and assessments for participants are shown in Fig. 3. Follow up will continue for 12 months. Participants in the intervention group will perform SSE and submit images at baseline (post-randomisation), 3, 6, 9, and 12 months post randomisation. Outcomes will be assessed by participant-reported questionnaires at baseline (pre-randomisation), 6 and 12 months after randomisation.

**Fig. 3 Fig3:**
[figure not shown]
Participant schedule

### Sample size {14}

Assuming that 6–8% of patients in the clinician-led surveillance group have a subsequent new primary or recurrent melanoma diagnosed within the 12 months follow up [21, 45] and that 1% have a diagnosis through a fast-tracked unscheduled clinic visit, we will need to recruit at least 452 participants (226 to patient-led surveillance and 226 to clinician-led surveillance) in order to have at least 80% power to detect a 5% absolute increase in the patient-led surveillance group (i.e. 6% have new or recurrent melanoma diagnosed through unscheduled visit at treatment centre). Assuming up to 25% of study participants withdraw consent or dropout, we will recruit 600 participants (300 to patient-led surveillance and 300 to clinician-led surveillance). These calculations assume a two-sided 5% significance level and were done using Fisher’s exact test. This sample size will also ensure at least 80% power to detect a hazard ratio of 1.71 for time from randomisation to diagnosis of a skin cancer for the patient-led vs clinician-led surveillance groups (due to earlier and increased detection in the patient-led group). This calculation assumes a 20% event rate in the clinician-led surveillance group [21, 45] (60 events among 300 control participants), a 32% event rate in the patient-led surveillance group (96 events among 300 intervention participants), and 26% event rate overall (156 events among 600 trial participants).

For the nested qualitative study, we will aim to recruit 30–45 participants, which may vary depending on the saturation of themes but is a sample size commonly sufficient to reach saturation in themes and topics [46].

### Recruitment {15}

Strategies for achieving adequate participant enrolment include training and support for clinical staff at each site, provision of one-page flyers for patients in clinic waiting rooms, provision of one-page summary of the trial tasks for recruiting clinicians, and regular monitoring of recruitment targets. Administrative data from the Melanoma Institute Australia (MIA), indicates that approximately 800–900 new patients are treated for early melanoma at MIA each year and approximately 50% then attend regular follow-up at MIA (includes MIA clinics in North Sydney and Royal Prince Alfred Hospital clinics) [47]. The pilot trial found that 21% of people screened were randomised [33]. Thus, recruiting 600 patients over 2 years from all patients with a history of early melanoma who are attending follow-up (new and existing patients) at MIA, Royal Prince Alfred Hospital or the GP-run Newcastle Skin Check clinics appears feasible.

### Assignment of interventions: allocation

#### Sequence generation {16a}

Participants will be randomly assigned to either control or intervention arms with a 1:1 allocation ratio. Minimisation will be used to ensure the study groups are balanced on key prognostic factors:
Specialist versus GP led clinic (two specialist clinic sites = Melanoma Institute Australia/Royal Prince Alfred Hospital and one GP led site Newcastle Skin Check)Patient age (age groups = 18–39, 40–70, 71+)Gender (male, female, other)Melanoma stage (Stage 0, IA, IB, IIA, IIB, IIC)Risk of a subsequent new primary melanoma (1-year absolute risk score < 5%, 5–10%, > 10% [48]).Dysplastic naevus syndrome (yes or no).

Within the intervention arm, participants will be randomised 1:1 to one of the two models of mobile dermatoscope (see Fig. 4). The method of randomisation to type of device will be by permuted blocks of varying size and stratified by key variables that might influence adherence with the device (potential confounders for the secondary outcome being evaluated for this comparison): site, age, and gender. The ratio will be adapted depending on adherence with submission of images that are of sufficient quality for teledermatology reporting. After 60 participants have been randomised into the intervention group, we will measure the proportion of intervention participants who have had an image reported on at one month after their baseline images (post randomisation) were due. If there is > 30% absolute difference in the proportion of intervention participants who have had an image reported on, participants who are subsequently enrolled will be randomised 2:1 to the dermatoscope model where more participants had an image reported on. If there is > 50% absolute difference in the proportion of intervention participants who have had an image reported on, then all participants who are subsequently enrolled will be randomised to dermatoscope model where more participants had an image that was reported on.

**Fig. 4 Fig4:**
[figure not shown]
Two-stage randomisation in MEL-SELF trial. *Polarised device refers to cross-polarised light dermatoscope, and non-polarised device refers to natural light dermatoscope

### Concealment mechanism {16b}

Participants will be randomised using the University of Sydney’s NHMRC Clinical Trials Centre’s Interactive Voice Response System (IVRS) which is a centralised telephone randomisation service. Allocation concealment will be ensured as the service will not provide the randomisation code until the patient has been recruited into the trial.

### Implementation {16c}

After participants have successfully completed the active run-in phase, the site coordinator will telephone the IVRS to perform random allocation and record the assigned treatment arm. The site coordinator will then distribute control and intervention packages to the participants.

### Assignment of interventions: blinding

#### Who will be blinded? {17a}

Blinding of participants, site staff and treating clinicians will not be possible in this trial. However, the teledermatologist who assesses the images submitted by participants in the intervention group will be blinded to the patient’s identity. For the primary outcome, the trial dermatopathologist will review the histopathology of all new melanoma diagnoses made during follow up blinded to study group allocation, and the endpoint adjudication committee will review the classification of clinic visit as routinely scheduled or as fast-tracked unscheduled blinded to study group allocation. Where possible, the endpoint adjudication committee will also review other secondary outcomes, blinded to study group allocation.

#### Procedure for unblinding if needed {17b}

The design is open label with only outcome assessors being blinded so unblinding will not occur.

### Data collection and management

#### Plans for assessment and collection of outcomes {18a}

##### Demographic and clinical information

At baseline, demographic and other risk factor information including age, sex, Indigenous status, non-English language background, marital status, children, occupation, income, highest education level, postcode, brand of smartphone owned, baseline use of digital technology/internet, risk of a subsequent new primary melanoma and keratinocyte cancer [48–50] and personal history of diagnosed depression or anxiety will be collected using standardised items from the Australian Census questionnaire and other instruments, where appropriate. Clinical information including time since first melanoma diagnosis, and characteristics of prior melanoma(s) including AJCC sub-stage and site, will be retrieved from administrative datasets at the clinics.

##### Questionnaires

During the active run-in phase participants will complete a baseline questionnaire and follow up questionnaires will be completed at 6 months and 12 months after randomisation. These questionnaires will collect data on SSE practice and beliefs [42], level of fear of new or recurrent melanoma [10], general stress, anxiety and depression (DASS-21) [43] and acceptability of reducing scheduled clinic visit frequency. Participants will complete questionnaires online through REDCap. Access codes and reminders will be sent to participants via email and SMS.

